## Evaluation endpoints

## Primary evaluation endpoint

The primary evaluation endpoint is the average change in the LDQ from baseline after 12 weeks of oral administration of the investigational product.

Before investigational product administration, the total LDQ score will be categorized into three groups (No / Very Mild: 0-8; Mild / Moderate: 9-24; Severe / Very Severe: 25-40), and the average change in the LDQ from baseline will be calculated for each group.

## Secondary evaluation endpoint

- Average LDQ after 12 weeks of oral administration of the investigational product.
- Average change in the GSRS from baseline after 12 weeks of oral administration of the investigational product.
- Incidence rate of GI adverse events (dyspepsia, diarrhea, nausea, abdominal pain, heartburn) after 12 weeks of oral administration of the investigational product.
- Discontinuation rate due to GI adverse events after 12 weeks of oral administration of the investigational product.
- Average change in the pain VAS from baseline after 12 weeks of oral administration of the investigational product.
- Average change in the average EQ-5D score from baseline after 12 weeks of oral administration of the investigational product.
- Drug compliance after 12 weeks of oral administration of the investigational product.
- Ancillary and rescue drug use after 12 weeks of oral administration of the investigational product: average number of days used, average daily amount used (total amount used / total number of days used), and average amount of use during study participation (total amount used / study duration).
- Incidence, frequency, and characteristics (clinical presentation, severity, result, etc.) of adverse events after 12 weeks of oral administration of the investigational product.
- Results of physical examination, vital signs, and laboratory tests after 12 weeks of oral administration of the investigational product.

## Other evaluation endpoints

N/A

## Definition of analysis sets

#### Target population

This study will be conducted on osteoarthritis patients of ≥50 years who can perform normal physical activity during the study period, with a pain VAS of 40 mm or more.

**Safety evaluation set: A population in which at least one safety follow-up observation is made after randomization and investigational product administration.**

**Full Analysis (FA) set: A population in which at least one efficacy evaluation is performed after randomization and investigational product administration.**

**Per-Protocol (PP) set: A population in which at least one efficacy evaluation is performed after randomization and investigational product administration, and in which there is no major protocol violation (violation of inclusion / exclusion criteria, violation of compliance). A compliance rate of 80% is used as the reference.**

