# Synopsis

| Trial Title | A prospective, randomized, double-blind, double-placebo, active-controlled, multicenter, interventional study to compare the gastroprotective and pain-relieving effects of Naxozol and celecoxib in patients with osteoarthritis | | |
| --- | --- | --- | --- |
| Trial Number | Naxozol_P4_1 | Version | 1 |
| Sponsor | [name] (Severance Hospital, Department of Orthopedics) | | |
| Phase | Phase 4 (investigator-initiated trial) | | |
| IND | Applicable [figure not shown] Not applicable | | |
| Institutions / Countries | 10 institutions / Korea | | |
| Expected duration of study | Approximately 24 months after study initiation | | |
| Purpose | **Primary Purpose**  To prove non-inferiority of the gastroprotective effect of a 12-week administration of Naxozol to osteoarthritis patients compared to that of celecoxib, as evaluated by the Leeds Dyspepsia Questionnaire (LDQ).  **Secondary Purpose**   - To compare the gastroprotective effect, as evaluated by the Gastrointestinal Symptom Rating Scale (GSRS), of 12 weeks of treatment of osteoarthritis patients with Naxozol or celecoxib. - To compare the incidence rate of gastrointestinal (GI) adverse events, as well as the drug discontinuation rate due to gastrointestinal (GI) adverse events, after 12 weeks of treatment of osteoarthritis patients with Naxozol or celecoxib. - To compare the pain improvement effect, as evaluated by the visual analogue scale (VAS), of 12 weeks of treatment of osteoarthritis patients with Naxozol or celecoxib. - To compare the improvement in quality of life (QoL), as evaluated by EQ-5D, of 12 weeks of treatment of osteoarthritis patients with Naxozol or celecoxib. - To compare patient compliance during 12 weeks of treatment of osteoarthritis patients with Naxozol or celecoxib. - To compare overall safety of Naxozol and celecoxib after 12 weeks of treatment of osteoarthritis patients. | | |
|  |  |  |  |
|  |  |  |  |

| Planned study design | Prospective, randomized, double-blind, double-placebo, active-controlled, two-arm, parallel, multi-center trial. |
| --- | --- |
| Expected number of study subjects | A minimum of 106 (53 in experimental group, 53 in control group), considering a 20% discontinuation rate, with the final aim of 42 subjects in each of the two groups. |

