#### Expected duration of the study

- The expected duration of the subject enrolment period is approximately 21 months.
- The expected duration of the study is approximately 12 weeks from the study initiation date.
- The planned treatment and evaluation period for each subject consists of one day of screening and washout (day of administration) and 12 weeks of treatment and follow-up.
- Each subject will undergo 1 screening visit, 1 randomization and investigational product distribution visit, and 1 follow-up visit.

The general structure of the study is as follows (Figure 1):

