## Termination of study

In this study, Visit 3 is defined as the “end of study (trial) visit’, and subjects who have completed Visit 3 are defined as completed subjects. If the following situations occur, this study will not be deemed completed:

- - There are remaining subjects who are still due to receive investigational products.
  - The pre-specified visit schedule at a study site has not been completed.

If a subject misses a visit or is lost to follow-up despite reasonable requests for a visit, the corresponding subject will be deemed to have terminated the study participation. No further evaluation will be conducted after study termination.

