## Evaluation schedule

A general summary of the study procedure is shown in the study flow chart (Appendix 1). All visits must be conducted according to the pre-determined schedule. The study duration for each subject is 12-14 weeks and consists of the following evaluations:

- - Screening and washout period: 0 - 2 weeks (Day -14 - Day 1).
  - Treatment & F/U period: 12 weeks (Day 1 - Day 84).

The visit schedule during the study consists of 3 visits, including 1 pre-treatment screening visit. Randomization and study drug distribution will be conducted at visit 2, and the last visit will be conducted 12 weeks after the first day of the investigational product administration.

Additional visits may be conducted if adverse events occur.

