## Statistical analysis plan

## General considerations

Efficacy data obtained from the subjects in this study will be analyzed in the FA and PP sets. Safety data will be analyzed in the Safety evaluation set. Considering that this is a non-inferiority study, the primary efficacy endpoint will be analyzed in both the FA and PP sets, according to ICH guidelines.

All statistical sets, excluding the primary efficacy endpoint, will be subjected to two-sided tests with a significance level of 5%.

Missing data will be replaced using a multiple imputation method. No interim analysis will be performed.

Co-administered drugs will be recorded in ATC terminology, and adverse events and medical history will be standardized to SOC (system organ class) and PT (preferred term) using a Medical Dictionary (MedDRA or WHOART).

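### Both primary analysis sets exclude any drop-out who gives no early-termination LDQ, and the stated imputation cannot reach those subjects, so the non-inferiority test can be biased if drop-out depends on dyspepsia

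*Protocol*

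**What the plan says.** Section 7.4 defines the FA set as "A population in which at least one efficacy evaluation is performed after randomization and investigational product administration". The PP set repeats that condition and adds a second: "and in which there is no major protocol violation (violation of inclusion / exclusion criteria, violation of compliance", with 80% compliance as the threshold. The Synopsis gives the same definitions. Both sets carry the primary test: section 7.5.1 states that "the primary efficacy endpoint will be analyzed in both the FA and PP sets, according to ICH guidelines".

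Section 6.1 says "The visit schedule during the study consists of 3 visits, including 1 pre-treatment screening visit", and section 4.1 says "Each subject will undergo 1 screening visit, 1 randomization and investigational product distribution visit, and 1 follow-up visit". The LDQ is taken at Visit 2 as baseline and at Visit 3 in week 12, so one post-baseline LDQ is scheduled.

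Drop-outs are to have the Visit 3 assessments where this can be done (sections 4.1 and 4.5.1), and the early-termination visit in section 6.1 lists the LDQ. A subject who misses a visit or is lost is treated under section 4.9 as having ended participation: "No further evaluation will be conducted after study termination".

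On missing data, section 7.5.1 says "Missing data will be replaced using a multiple imputation method". It names no population, and the protocol does not say whether an early-termination LDQ stands as the week-12 value or is replaced by an imputed one. The sample size is set "considering a 20% discontinuation rate, with the final aim of 42 subjects in each of the two groups".

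**The concern.** Entry to the FA set depends on having a post-baseline outcome, and the schedule offers only one apart from an early-termination visit that may not happen. A drop-out without that visit is in neither primary set. Multiple imputation fills gaps for subjects inside a set, so it does not reach them. Analysing both FA and PP gives no protection, because the two sets share the exclusion.

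The excluded subjects may well be informative. Section 5.3.5.1 names dyspepsia and abdominal pain as the commonest adverse events leading to discontinuation of celecoxib. Section 5.3.4.1 lists dyspepsia as very common on the experimental drug. GI discontinuation is itself a compared endpoint (section 7.3.2). The symptom that may drive drop-out is the one the primary endpoint measures. At the null boundary, where Naxozol is worse by 0.40, a common rule linking drop-out to a subject's own LDQ change removes more subjects from the Naxozol arm and shrinks the estimated difference. In a non-inferiority trial that error favours the claim.

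**Working it through.** **Inputs from the protocol.** SD 0.65, margin 0.40, one-sided α 0.025, power 80%, drop-out 20% (section 7.1); 1:1 allocation (section 7.2).

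**Assumptions, not in the protocol.** The share *e* of drop-outs who give an early-termination LDQ; the strength of the link between drop-out and LDQ; drop-out by arm.

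**1. The plan's own figures.** n = 2 × 0.65² × (1.96 + 0.842)² / 0.40² = 41.46, rounded up to 42. Then 42 / 0.80 = 52.5, rounded up to 53. Both reproduce.

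**2. Who is in the FA set.** Per arm, FA = 53 × (0.80 + 0.20*e*).

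| *e* | FA per arm | Non-completers in FA | Excluded | Completers as share of FA |
|---|---|---|---|---|
| 0% | 42.4 | 0.0 | 10.6 | 100% |
| 25% | 45.1 | 2.7 | 8.0 | 94% |
| 50% | 47.7 | 5.3 | 5.3 | 89% |
| 75% | 50.4 | 8.0 | 2.7 | 84% |
| 100% | 53.0 | 10.6 | 0.0 | 80% |

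The PP set is narrower. Compliance is actual over planned administrations, and 0.80 × 84 = 67.2 days. If planned administrations cover the full 84 days, a subject who stops before about day 67 fails PP even with an early LDQ.

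**3. Direction and size by arithmetic.** Let drop-outs average *k* points worse in LDQ change than completers, with drop-out rates d_T (Naxozol) and d_C (celecoxib). Within FA, the share of non-completers in each arm is p = d*e* / (1 − d + d*e*). Bias = *k*(p_T − p_C) − *k*(d_T − d_C). At a true difference of 0.40, type I error = Φ(−bias/SE − 1.96), with SE = 0.65 × √(1/n_T + 1/n_C).

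Example: 25% against 15%, *k* = 1, *e* = 0. Bias = −(0.25 − 0.15) = −0.10. n_T = 53 × 0.75 = 39.75 and n_C = 53 × 0.85 = 45.05, so SE = 0.141. Error = Φ(0.707 − 1.96) = 10.5%.

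| Drop-out, Naxozol / celecoxib | *k* | *e* | Bias | Type I error |
|---|---|---|---|---|
| 20% / 20% | any, equal in both arms | 0 or 50% | 0 | 2.5% |
| 25% / 15% | 0.5 | 0 | −0.05 | 5.4% |
| 25% / 15% | 1 | 0 | −0.10 | 10.5% |
| 25% / 15% | 1 | 50% | −0.04 | 4.7% |
| 15% / 25% | 1 | 0 | +0.10 | 0.4% |

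**4. Simulation with one drop-out rule for both arms.** 53 per arm, LDQ change N(0.40, 0.65²) against N(0, 0.65²), P(drop-out) = expit(a + b × change), and *a* set for 20% overall. The odds ratio per SD is exp(0.65b): about 1.9, 3.7 and 7.0 for b = 1, 2 and 3. An early LDQ, where given, is taken to equal the week-12 value. Ranges cover independent runs.

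| Type I error | OR 1.9 | OR 3.7 | OR 7.0 |
|---|---|---|---|
| No drop-out gives an early LDQ | 3.2–3.8% | 6.8–7.2% | 11.1–11.4% |
| Half do | 2.8–3.0% | 3.6–3.9% | 4.5% |
| Three quarters do | 2.7% | 3.0% | 3.4% |

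With no early LDQ, drop-out is about 23% against 17%, 25% against 15% and 26% against 14%, and the mean estimate falls from 0.40 to about 0.375, 0.338 and 0.307. With b = 0 the error is nominal within simulation error.

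**5. What a remedy achieves, with no early LDQ.**

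| Analysis in all dosed subjects | OR 1.9 | OR 3.7 | OR 7.0 |
|---|---|---|---|
| Imputation by arm only, missing at random | 3.4% | 6.8% | 11.4% |
| Imputation adding an assumed GI adverse event flag | 2.7% | 5.5% | 8.2% |
| Adding 0.40 to imputed Naxozol values | 0.6% | 1.1% | 2.1% |

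**The case against.** The protocol has a safeguard. The early-termination visit names the LDQ, and section 4.5.2 asks for observations after product discontinuation as for withdrawal. A subject who stops for dyspepsia and attends is in the FA set, with a questionnaire covering the last four weeks. This stands: attendance limits the problem, and the protocol gives no basis for predicting it.

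A reader might infer that both primary sets are in effect completer sets with almost nobody left to impute. For the FA set that follows only if few attend. Attendees still lack a true week-12 value and could be imputed. Nor does the target of 42 per arm show that completers are what will be analysed; it is ordinary inflation for drop-out and says nothing about set membership.

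A reader might also infer that bias towards non-inferiority is established. The documents give no GI drop-out rate by arm. The one discontinuation rate quoted, 7.1% for adverse events on celecoxib against 6.1% on placebo (section 5.3.5.1), is about a third of the assumed 20% and covers all adverse events. Almagate is also supplied for severe dyspepsia. The odds ratios are scenarios.

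Finally, outcome-dependent missingness causes the inflation, and rewording the set does not cure it alone. That is correct, as step 5 shows. The wording still matters, because imputation and sensitivity analyses cannot act on subjects outside the set. Imputation detail can be left to a statistical analysis plan, but this set definition is fixed in the protocol.

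**Conclusion.** The point holds in conditional form. As written, both primary sets exclude every drop-out without an early-termination LDQ, up to about 10.6 per arm at 20% drop-out, and the stated imputation cannot reach them. If drop-out depends on dyspepsia and Naxozol is truly worse, one-sided type I error is about 3 to 11% with no early LDQs and about 3 to 4.5% if half of drop-outs give one, against 2.5% nominal. These figures rest on assumed odds ratios of about 1.9 to 7 per SD and on early values equal to week-12 values. The bias vanishes if drop-out is unrelated to LDQ and reverses if drop-out is worse on celecoxib. This should be fixed; confidence is moderate, because neither attendance nor the drop-out pattern is known.

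**What to change.** The changes work as a package:

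- In section 7.4 and the Synopsis, define the FA set as all randomised subjects who took at least one dose, with no post-baseline requirement.
- Impute missing week-12 LDQ within that set using arm, baseline LDQ, any early-termination LDQ, and GI adverse event or discontinuation status. Imputation by arm alone does not remove the bias.
- State whether an early-termination LDQ is used as the week-12 value or as a predictor in the imputation.
- Add a delta-adjusted sensitivity analysis that worsens imputed Naxozol values over a range up to the 0.40 margin. Keep it out of the primary test: with no outcome dependence, the full 0.40 shift lowers the error to about 0.5%, which is over-conservative.
- Seek the Day-84 LDQ from subjects who stopped drug but still consent, and align section 4.9 with this. Values not collected at the time cannot be recovered.

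The cost is a wording change, one sensitivity analysis, a few extra questionnaires and a slightly wider interval. The analysis changes should be fixed before unblinding.

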## Statistical analysis plan

## General considerations

Efficacy data obtained from the subjects in this study will be analyzed in the FA and PP sets. Safety data will be analyzed in the Safety evaluation set. Considering that this is a non-inferiority study, the primary efficacy endpoint will be analyzed in both the FA and PP sets, according to ICH guidelines.

All statistical sets, excluding the primary efficacy endpoint, will be subjected to two-sided tests with a significance level of 5%.

Missing data will be replaced using a multiple imputation method. No interim analysis will be performed.

Co-administered drugs will be recorded in ATC terminology, and adverse events and medical history will be standardized to SOC (system organ class) and PT (preferred term) using a Medical Dictionary (MedDRA or WHOART).

## Primary outcome analysis

Average change in LDQ from baseline after 12 weeks of oral administration of the investigational product: descriptive statistics (sample size, mean, standard deviation, median, min, max) will be presented for LDQ change after 12 weeks of investigational product administration in each treatment arm. To prove non-inferiority of the experimental drug, the one-sided 97.5% confidence interval for the between-group difference in LDQ change will be calculated. If the 97.5% upper confidence limit is smaller than the non-inferiority margin of 0.40, the null hypothesis is rejected, and non-inferiority is proven. Additionally, before investigational product administration, the total LDQ score will be categorized into three groups (No / Very Mild: 0-8; Mild / Moderate: 9-24; Severe / Very Severe: 25-40) for further analysis.

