## Demographic information and other baseline evaluations

Demographic and other baseline information, including the following variables, will be evaluated:

- - Demographic information, such as age and gender.
  - Information regarding health status, such as current and past medical history.
  - Past and present medication history (including co-administration of low dose aspirin).
  - Participation in other clinical trials (within 30 days of screening).
  - Weight.
  - Surveys related to efficacy evaluation (LDQ, GSRS, pain VAS, and EQ-5D).

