#### Rationale:

The purpose of this study is to show the non-inferiority of the gastroprotective effect of Naxozol in osteoarthritis patients compared to that of celecoxib, as evaluated by the average change in the LDQ (Leeds Dyspepsia Questionnaire) score from baseline after 12 weeks of oral administration.

In previous studies that evaluated the symptomatic improvement of gastrointestinal disorders with a Likert scale such as the LDQ, 0.40 was used as the minimal clinically important difference (MCID) in the degree of improvement.(30, 31, 32) Hence, the non-inferiority margin for this study was also set at 0.4. The LDQ consists of a 5-step Likert scale.

In a study by Holtmann et al. on the efficacy of Itopride in the improvement of functional dyspepsia, the standard deviation of the average change in the LDQ was 0.63 - 0.65. In this study, the standard deviation (σ) was set at 0.65 for a more conservative approach. (22)

With a power of 80% and a one-sided α of 0.025, the number of subjects per treatment arm, as estimated by the sample size derivation formula below, was 42. Considering a drop-out rate of 20%, this study will enroll 53 subjects per treatment arm (106 in total).

𝑛experimental

2

= 𝑛control =

[2𝜎2][𝑍_𝛼_

δ2

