### + 𝑍_𝛽_]

[2 ∗ 0.652][1.96 + 0.842]2

= 0.42 ≅ 42

σ= standard deviation of change in LDQ

δ = non-inferiority margin

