- The average change in pain VAS from baseline after 12 weeks of oral administration of the investigational product: descriptive statistics (sample size, mean, standard deviation, median, min, max) for pain VAS before and after 12 weeks of investigational product administration, and the change in pain VAS from baseline after 12 weeks of oral administration of investigational product in each treatment arm, will be presented. The change within each arm will be tested for significance using the paired t-test or the Wilcoxon signed rank test. The between-group difference at each time point and in the amount of change will be tested for significance using the independent two-sample t-test or the Wilcoxon rank sum test.
- The average change in the average EQ-5D score from baseline after 12 weeks of oral administration of the investigational product: descriptive statistics (sample size, mean, standard deviation, median, min, max) for EQ-5D before and after 12 weeks of investigational product administration and the change in EQ-5D from baseline in each treatment arm will be presented. The change within each arm will be tested for significance using the paired t-test or the Wilcoxon signed rank test. The between-group difference at each time point and in the amount of change will be tested for significance using the independent two-sample t-test or the Wilcoxon rank sum test.
- Drug compliance after 12 weeks of oral administration of the investigational product: compliance during the 12 weeks of investigational product administration is defined by ‘actual number of administrations / predicted number of administrations *100’, and descriptive statistics (sample size, mean, standard deviation, median, min, max) will be presented for each treatment arm. The between-group difference in compliance will be tested for significance using the independent two-sample t-test or the Wilcoxon rank sum test. The actual number of administrations is determined based on the number of returned investigational products. Evident reasons, such as loss or damage, will be accounted for.

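### The primary non-inferiority comparison names no baseline covariate although baseline LDQ is scheduled for every randomized subject; it is valid, but generally less precise than a baseline-adjusted comparison

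*Protocol*

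**What the plan says.** **Primary analysis (Protocol, 7.5.2).** Change in LDQ is described by arm, and then: "To prove non-inferiority of the experimental drug, the one-sided 97.5% confidence interval for the between-group difference in LDQ change will be calculated". Non-inferiority is declared if the upper limit lies below 0.40. No test, model or covariate is named. Baseline LDQ enters only as three bands of the total score (0–8, 9–24, 25–40) for a further analysis.

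**Baseline data (6.1 and 6.2).** LDQ is administered at Visit 2, before randomization in the listed order of procedures. The baseline evaluations include "Surveys related to efficacy evaluation (LDQ, GSRS, pain VAS, and EQ-5D".

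**Secondary outcomes (7.5.3).** For GSRS, pain VAS and EQ-5D the tests are named and carry no covariate. The difference between groups "in the amount of change will be tested for significance using the independent two-sample t-test or the Wilcoxon rank sum test".

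**Sample size (7.1).** "With a power of 80% and a one-sided α of 0.025, the number of subjects per treatment arm" comes to 42. The margin and SD are given as follows: "Hence, the non-inferiority margin for this study was also set at 0.4" and "In this study, the standard deviation (σ) was set at 0.65 for a more conservative approach". The legend to the formula reads "σ= standard deviation of change in LDQ" and "δ = non-inferiority margin". The trial is therefore sized on an unadjusted two-sample comparison of change.

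**The concern.** Subtracting baseline fixes the coefficient on baseline at 1. ANCOVA estimates that coefficient from the data. Unless the true slope of week-12 score on baseline score is 1, the change-score difference carries avoidable variance.

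Two features of this trial make the point worth raising. There is no LDQ entry criterion, so baseline scores may vary widely. Randomization is blocked by site but not stratified by baseline severity, so chance differences in baseline LDQ are left to the analysis.

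At stake is the width of one interval. The trial has a single confirmatory comparison, planned at 80% power, to be examined in both the FA and PP sets.

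**Working it through.** **Inputs from the protocol (7.1, 7.2).** Margin δ = 0.40; SD of change σ = 0.65; one-sided α = 0.025; power 80%; 1:1 allocation; 20% drop-out. The true difference is taken as 0, because the denominator of the formula is the margin alone.

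**Step 1: reproduce the plan's figure.**
- n per arm = 2σ²(1.96 + 0.842)²/δ² = 2 × 0.4225 × 7.851/0.16 = 41.46, rounded up to 42.
- Enrolled: 42/0.80 = 52.5, rounded up to 53 per arm, 106 in total.
- SE of the difference at 42 per arm = 0.65 × √(2/42) = 0.142.
- δ/SE = 2.82. Power is 80.5% by the normal approximation and 79.6% by noncentral t with 82 df.

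The plan's numbers are right for the comparison that it describes.

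**Step 2: effect of baseline adjustment.** Let r be the correlation between baseline and week-12 LDQ, and k the ratio of the week-12 SD to the baseline SD. Then

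ANCOVA variance / change-score variance = k²(1 − r²)/(1 + k² − 2rk).

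With k = 1 this is (1 + r)/2. The SD that drives power becomes 0.65 × √ratio. **Neither r nor k is given in the protocol; all values below are assumptions.** Power is by noncentral t with 81 df at 42 per arm.

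Equal SDs (k = 1):

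| r | variance ratio | effective SD | power |
|---|---|---|---|
| no adjustment | 1 | 0.650 | 79.6% |
| 0.3 | 0.65 | 0.524 | 93.3% |
| 0.5 | 0.75 | 0.563 | 89.6% |
| 0.7 | 0.85 | 0.599 | 85.6% |
| 0.9 | 0.95 | 0.634 | 81.6% |

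Unequal SDs, power by r:

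| k | r = 0.3 | r = 0.5 | r = 0.7 |
|---|---|---|---|
| 0.75 | 98.4% | 97.2% | 96.1% |
| 1.25 | 88.2% | 83.9% | 80.3% |
| 1.5 | 84.7% | 81.0% | 79.7% |

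The gain all but vanishes at k = 1.5 and r = 0.7. There the slope rk is 1.05, close to the value of 1 that the change score imposes.

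**Step 3: chance imbalance (k = 1).** The baseline SD is 0.65/√(2(1 − r)). A one-SE difference in baseline means moves the change-score difference by baseline SD × √(2/42) × (1 − r):
- r = 0.3: 0.549 × 0.218 × 0.7 = 0.084, or 21% of the margin;
- r = 0.7: 0.839 × 0.218 × 0.3 = 0.055, or 14% of the margin.

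This variation is part of the SE of 0.142 in Step 1. It is the part that adjustment removes, not something to be added to it.

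**The case against.** **The planned comparison is not an error.** A difference in change scores is unbiased under randomization and holds its type I error. Endpoint, interval and sample size all use the same change score, and the stated power is delivered. This stands in full. A reader might infer that the primary analysis is biased or underpowered; the documents do not support that. Nor is the imbalance shift of 0.05–0.08 an extra bias, since the interval already allows for it.

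**The primary section never says unadjusted.** An ANCOVA of change also gives a between-group difference in LDQ change, and covariates are often left to a separate analysis plan, which is not at hand. This stands in part. A reader might infer that the protocol rules out adjustment; it does not. Still, Section 7 assigns methods endpoint by endpoint. It names GEE models for physical examination and laboratory findings, names unadjusted tests for the secondary change scores, and sizes the trial on the SD of change. An unadjusted comparison is the natural reading, and at best the estimator behind the only confirmatory decision is left open.

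**The size of the gain is not known.** This stands. It is tempting to say that ANCOVA would raise power to 86–93%, but that range needs a correlation of 0.3–0.7 and equal SDs. Unequal SDs are plausible in either direction. The exclusion of known reflux disease and of recent or active ulcer, with no minimum LDQ, may leave baseline scores low; yet Section 4.1 expects scores to fall.

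**Extending ANCOVA to the secondary outcomes could remove the rank-test option for skewed scores.** This stands, and the fix keeps that option.

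**Conclusion.** The point holds as a missed gain in precision that is worth taking, not as a flaw in validity. The primary comparison is specified as a difference in LDQ change with no baseline covariate, although the covariate is already collected.

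In large samples, ANCOVA is never less precise than the change-score comparison, and here it costs one degree of freedom. Its benefit ranges from almost nothing to a substantial rise in power, depending on r and k as tabulated above. The 86–93% figure is one conditional part of that range.

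All power figures also assume that the margin of 0.40 and the SD of 0.65 are on the scale of the LDQ score analysed. Sections 7.3.1 and 7.5.2 also use a total score of 0–40, so that scale needs to be stated.

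**What to change.** Before unblinding, amend 7.5.2 along these lines:

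- The primary estimate is the treatment difference (experimental minus control) from an ANCOVA of week-12 LDQ change on treatment, with baseline LDQ as a continuous covariate.
- Non-inferiority is concluded if the one-sided 97.5% upper limit of that difference is below 0.40, examined in both the FA and PP sets.
- The LDQ score analysed is stated to be on the same scale as the margin of 0.40 and the SD of 0.65.

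In 7.5.3, the same adjustment may be used for GSRS, pain VAS and EQ-5D change, keeping a rank-based option for skewed scores.

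The sample size can stay at 42 evaluable and 53 enrolled per arm. Because r and k are unknown, the possible gain should not be used to reduce it. The cost is a change of wording and one degree of freedom, with no new data, visits or subjects.

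### The primary test compares LDQ change with 0.40 without fixing the LDQ scale; on the only score given a range, the 0-40 total, power could be roughly 5-17% instead of 80%

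*Protocol*

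**What the plan says.** **Margin and SD.** The rationale in section 7.1 takes the margin from earlier symptom studies on Likert-type scales, where "0.40 was used as the minimal clinically important difference (MCID) in the degree of improvement". It continues: "Hence, the non-inferiority margin for this study was also set at 0.4. The LDQ consists of a 5-step Likert scale". For variability it cites an itopride trial in functional dyspepsia, in which "the standard deviation of the average change in the LDQ was 0.63 - 0.65", and then states: "In this study, the standard deviation (σ) was set at 0.65 for a more conservative approach". These inputs give 42 evaluable subjects per arm and 53 enrolled.

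**Instrument.** Section 6.4.1 lists eight symptoms, each graded in five steps of severity. Appendix 2 puts a yes/no question before each grading. Neither place assigns numbers to the answers.

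**Endpoint and test.** Section 7.3.1 and the synopsis word the primary endpoint as the average change in the LDQ from baseline. Section 7.5.2 applies the rule: "If the 97.5% upper confidence limit is smaller than the non-inferiority margin of 0.40, the null hypothesis is rejected, and non-inferiority is proven". The synopsis repeats the rule.

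**The one score with a range.** Sections 7.3.1 and 7.5.2 also say that, before dosing, "the total LDQ score will be categorized into three groups (No / Very Mild: 0-8; Mild / Moderate: 9-24; Severe / Very Severe: 25-40". In 7.5.2 this stands in the same paragraph as the 0.40 rule.

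**The concern.** A non-inferiority margin has meaning only in the units of the variable tested. Here the margin and SD are argued on a scale of a few severity steps, while the only LDQ score whose range the protocol gives runs from 0 to 40. No sentence says whether the primary variable is the mean of the eight items or their sum.

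The wording of the endpoint does not settle it. The protocol uses the same average-change phrase for the pain VAS, a single line with no items to average, so there the average is taken across patients. For the EQ-5D it speaks separately of an average score. It has no such wording for the LDQ.

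The confirmatory conclusion is at stake. Two equally effective drugs would usually pass on the item mean. On the total with an unchanged margin they would probably fail.

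**Working it through.** **Inputs.** From section 7.1: one-sided α 0.025 (z = 1.96), power 80% (z = 0.842), margin δ = 0.40, SD σ = 0.65, drop-out 20%. The true difference is 0, implied because the formula divides by the margin alone. Allocation is 1:1 (section 7.2). There are eight items with five severity grades (section 6.4.1).

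**1. The plan's own figure.**

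n = 2σ²(zα + zβ)²/δ² = 2 × 0.65² × (1.96 + 0.842)²/0.40² = 41.46, so 42 per arm. Then 42/0.8 = 52.5, so 53 per arm and 106 in total. Both reproduce.

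Power = Φ(δ/SE − 1.96), with SE = σ√(2/n). At n = 42, SE = 0.65 × 0.2182 = 0.142, δ/SE = 2.82 and Φ(0.86) = 80.5% (79.6% with the noncentral t).

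**2. What the 0-40 range implies.** 40/8 = 5, so each item runs from 0 to 5 with no symptom scored 0. Scoring the five grades 1 to 5 with no zero would give a minimum of 8. On the total, 0.40/40 = 1% of the range, and 0.40/8 = 0.05 of a severity step per item.

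**3. Power on the total with the margin left at 0.40.** The documents give no total-score SD, so two readings of 0.65 are tried.

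*Reading A: 0.65 is the SD of the eight-item mean.* The total is 8 times the mean, so its SD is 8 × 0.65 = 5.2.
- SE = 5.2 × 0.2182 = 1.135; δ/SE = 0.352; Φ(0.352 − 1.96) = 5.4%.
- The 95% half-width is 1.96 × 1.135 = 2.22 points, more than five times the margin.
- For 80% power, n = 2 × 5.2² × 7.851/0.16, about 2,650 per arm.

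*Reading B: 0.65 is the SD of change in a single item.* With a common inter-item correlation ρ, the total SD is 0.65√(8 + 56ρ).

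| ρ | Total SD | Power at 42 per arm |
| --- | --- | --- |
| 0 | 1.84 | 16.8% |
| 0.3 | 3.24 | 8.2% |
| 0.5 | 3.90 | 6.8% |
| 1 | 5.20 | 5.4% |

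The range is therefore about 5% to 17% at 42 per arm. At all 53 per arm it is about 6% to 20%.

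**4. Rescaling margin and SD together.** Under Reading A the total-score equivalents are 8 × 0.40 = 3.2 and 8 × 0.65 = 5.2. Then n = 2 × 5.2² × 7.851/3.2² = 41.46, again 42 per arm with 80.5% power.

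**The case against.** The best defence is that the protocol never applies 0.40 to the total. The word total appears only where baseline severity is split into three groups, and in 7.5.2 that is introduced as an additional analysis. Section 7.1 is consistent within itself: margin and SD are presented together on a Likert-type scale, and 42 and 53 reproduce. On that scale the stated power stands. How items are combined is also often left to a statistical analysis plan, which is not available here.

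Much of this stands, and it rules out several stronger readings that a reader might infer:
- **That the trial has about 5% power.** This needs both that the total is tested and that its SD is about 5.2. The protocol states neither, and 5% is the low end of the range.
- **That 0.40 and 0.65 can only be item-scale figures.** This is a strong inference, but the cited trials cannot be checked here. If 0.65 were the SD of the total itself, the arithmetic would still give 80% power, though the typical spread in change would then be under one point on a 40-point score.
- **That each item is defined as 0-5.** This is inferred from 40/8 and is not written down.
- **That the scale will be chosen after unblinding.** Nothing in the protocol shows this.

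What does not stand is that the gap is only a detail for later. The protocol itself fixes the endpoint, margin, SD and decision rule, so it must state the units they share. The only scale whose range it gives does not fit the margin as argued.

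**Conclusion.** The point holds as an unfixed scale in the primary decision rule. On the item mean, the planned 80% power at 42 per arm is correct. On the 0-40 total with margin 0.40, power at 42 per arm would be roughly 5-17%. It would be 5.4% if 0.65 is the SD of the eight-item mean. If 0.65 is a single-item SD, it would run from about 17% down to 5% as inter-item correlation goes from 0 to 1. All these figures assume a true difference of zero, and the total-score SDs are assumptions.

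The documents do not show that the sample size is wrong, since any consistent rescaling of margin and SD returns 42 per arm. The correction is still needed, because the pass/fail result of the primary test can turn on a choice that the protocol leaves open.

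**What to change.** Before unblinding, amend sections 7.1, 7.3.1 and 7.5.2 and the synopsis to state:

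- **One primary LDQ score.** The natural choice is the mean of the eight items, range 0-5.
- **Item coding.** No symptom = 0, very mild = 1, and so on to very severe = 5, as the 0-40 range implies.
- **Direction.** Change is week 12 minus baseline and the difference is Naxozol minus celecoxib, so that higher is worse and an upper limit below a positive margin is the right test.
- **Margin and SD on that scale.** 0.40 and 0.65 for the item mean. The equivalents on the total are 3.2 and 5.2, provided the cited itopride trial confirms that 0.65 is the SD of the item mean.

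Keep the 0-8, 9-24 and 25-40 bands of the total for the baseline categories only.

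The cost is a wording amendment and one check of the cited source. If the check confirms the SD, no further patients, visits or data are needed and 42 evaluable (53 enrolled) per arm stands.
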